##### System integration—fNIRS, EEG and GRAIL

2.8.1.6

Synchronized timestamps are integral across all systems for seamless coherence and precision. Lab streaming layer (LSL) (Kothe et al., 2019) will be used to synchronize the different measurement systems, all sending their data via a local network generated by a Raspberry Pi (Raspberry Pi Foundation, United Kingdom). This setup was validated experimentally by our workgroup (Maas et al., 2024).

##### Screenings

2.8.1.7

Initial screenings will be conducted via telephone, including the prescribed eligibility criteria. On site, further screenings are undertaken by scientific staff: Part 3 of the MDS-Unified Parkinson’s Disease Rating Scale (MDS-UPDRS) (Goetz et al., 2008), the Montreal Cognitive Assessment (MoCA) (Nasreddine et al., 2005) and Freiburg Visual Acuity Test (Bach, 1996). The vibratory sensitivity will be measured with a 128 Hz Rydel-Seiffer tuning fork at the medial longitudinal arch of the foot, such as the medial cuneiform bone (Buchman et al., 2009; Hilz et al., 1998; Martina et al., 1998; Strzalkowski et al., 2015; Wolf et al., 2022).

Additionally, participants will be prompted to provide further behavioral and demographic information via questionnaire, encompassing details such as age, disease onset, medication type and dosage, social and cognitive activities of daily living as well as already existing experiences with cueing strategies or devices.

Further, participants will be asked to fill in the following questionnaire: Parkinson’s Disease Questionnaire (PDQ-39) (Jenkinson et al., 1997), New Freezing of Gait Questionnaire (NFOG) (Seuthe et al., 2021) and Godin-Shephard leisure-time Physical Activity Questionnaire (Godin, 2011). All questionnaires will be administered using the SoSci Survey platform (Leiner, 2024). The collected data will be used to provide a comprehensive description of the sample. Participants will have the option to complete the questionnaires on day 1. On day 2, all given answers will be checked for misunderstandings and clarified with the participant if necessary. In addition, further questionnaires will be handed to the participants on day 2 after all walking trials: System Usability Scale (Brooke, 1996) and a custom made questionnaire designed to gather participant recommendations for the vibrotactile prototype. All data will be assessed by experienced sport and exercise scientists.

#### Data preprocessing and analysis

2.8.2

##### EEG

2.8.2.1

EEG-Data will be preprocessed in MATLAB (MathWorks, Massachusetts, USA) using the BeMoBIL Pipeline, following the authors’ recommendations (Klug et al., 2022). Non-experimental segments will be removed using the synchronized start and end markers. The data will be resampled to 250 Hz and frequency specific noise will be removed using Zapline-plus with automatic noise frequency detection (Klug and Kloosterman, 2022). Bad channels (EEG channels with abnormal signal quality, indicated by low correlation with estimates derived from neighboring scalp electrodes) will be identified and interpolated. The data will be re-referenced to the average. For independent component analysis, the data will be high-pass filtered at 1.5 Hz for AMICA decomposition. The resulting ICs will be classified using the IClabel “lite” as classifier, with components showing a probability > 70% for muscle, eye, heart, line or channel noise being removed. The cleaned data will then be high-pass filtered at 0.2 Hz and subsequently be imported into MNE Python for further analysis (Gramfort et al., 2013). Morlet Wavelet analysis will be applied to extract the time-frequency components of interest within a 5-second time window preceding the FOG marker, effectively capturing the transition from regular locomotion to FOG. These extracted components will then be subjected to further statistical analysis.

##### fNIRS

2.8.2.2

Data analysis will be conducted using commonly used software, such as MNE Python (Gramfort et al., 2013). All raw data will be converted to the standardized *.snirf format, recognized for fNIRS data. Each dataset will be carefully reviewed to remove channels that do not meet the quality standards based on a signal quality index. This will include discarding channels that show a consistently low signal across significant portions of the recording sessions. Motion artifacts will be identified and corrected using typical correction methods such as spline interpolation and wavelet-based corrections, with specific thresholds for standard deviation and amplitude. Raw optical densities will be converted into changes in hemoglobin concentrations using the modified Beer-Lambert Law. This step will incorporate age and wavelength-specific differential pathlength factors to account for individual differences in optical properties. Slower systemic changes, often introduced by physical activities or head movements, will be mitigated by bandpass filtering and regressing out signals from short channels and specific head movement metrics. Finally, the signals from each channel will be normalized (z-transformed) to enable averaging and epoching across channels within the same cortical regions. This step ensures that the data are normally distributed, facilitating subsequent analysis. Spatial and temporal characteristics of the hemodynamic signal (e.g., peak amplitude, latency, etc.) related to FOG will be extracted and subjected to further statistical analysis.

##### Kinematics and kinetics

2.8.2.3

All gait parameters will be derived using customized scripts in commonly used software, such as MATLAB (MathWorks, Massachusetts, USA). In particular, heel-strike and toe-off times will be determined. Heel-strikes will be identified by analyzing the z-axis (up and down) of the heel markers, while toe-offs will be identified using the z-axis of the toe markers. The gait events’ exact timing will be calculated by identifying the corresponding inclines and declines in the force curves, utilizing the higher frequency of the force plates. The exact timing of the heel-strikes and toe-offs will then be used to calculate temporal aspects of the gait, like stance and swing time. Heel-strikes also represent the start and end of each gait cycle, therefore giving reverence points in continuous timeseries like joint angles. The computer controlling the treadmill will provide an export specifying the current velocity and distance covered at any given moment. Other gait parameters will be computed on a stride-by-stride basis using common operational definitions and will be calculated and exported for further analysis.

#### Data management

2.8.3

All collected data will be pseudonymized using coding lists. These lists are located in a locked cupboard within a locked room at the University of Münster. The coding lists will be destroyed after completion of data acquisition, ensuring the data will be anonymized from that point forward. Anonymized data will be stored for a minimum of 10 years on password protected servers of the University of Münster, limited to authorized researchers directly involved in data acquisition and analysis.

#### Statistical methods

2.8.4

To address our main research objectives, we will employ linear mixed effects models for our analyses. These models are well-suited for handling repeated measures and allow us to take advantage of the multi-trial data structure, while also accounting for both within-subject and between-subject variability. FOG episodes will be analyzed separately by motor context, distinguishing walking-FOG (forward locomotion, including doorway passage and straight walking) from turning-FOG (360° turning). Each FOG type will be compared against its corresponding unimpaired movement (Handojoseno et al., 2015a). The number of FOG episodes per type and participant will be reported.

First, we will identify cortical brain regions showing differential activation prior to the kinematic onset of FOG. Dependent variables include spatiotemporal characteristics of electrocortical and also hemodynamic brain activity that will be compared between FOG episodes and the corresponding period of unimpaired walking or turning. Second, we aim to delineate the neural signatures of FOG episodes, focusing on the temporal and frequency dynamics within the cortical areas of interest as defined by the first part of our analysis. This step includes analyzing the coherence of the neural dynamics across the brain regions involved. Lastly, we will examine if and how vibrotactile cueing may alter the neural signatures of FOG described above and whether it contributes to improved gait behavior when walking through virtual environments. This analysis will also focus on the reduction of the percentage time frozen, changes in kinematic and kinetic aspects of gait. All analyses will include relevant covariates, such as disease stage, motor symptom severity, prior experience with cueing and random effects accounting for inter-subject variability, and to investigate interindividual differences. To address the large number of comparisons across modalities, all analyses will include appropriate correction for multiple comparisons to control the rate of false-positive findings, using established methods such as Bonferroni correction or cluster-based permutation testing (Maris and Oostenveld, 2007).

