This research is motivated in particular by the limited evidence on the neural aspects of FOG and how effective countermeasures, such as vibrotactile cueing, can contribute to improvements of FOG related gait disturbances in everyday life. We will use a virtual walking scenario with automatic doorways to induce FOG to address three main research objectives. These objectives will focus on the neural mechanisms and pathways underlying FOG (RO1, RO2) and vibrotactile cueing (RO3). Our first research objective (RO1), aims to identify the cortical brain regions involved in FOG that show differential activation prior to the kinematic onset of FOG compared to normal, unimpaired walking. In the literature, the involvement of various brain regions such as frontal and central areas is reported (Asher et al., 2021; Cao et al., 2021; Handojoseno et al., 2015b; Shine et al., 2014). We expect involvement of similar brain regions (cf. perceptual dysfunction hypothesis (Bardakan et al., 2022)) in our virtual doorway scenario, but we also hypothesize differential activation based on the increased realism and environmental complexity achieved through the use of virtual reality. Second (RO2), we aim to delineate the neural signatures of induced FOG episodes, focusing on the temporal and frequency dynamics within the cortical areas of interest. Based on previous research we are expecting to see FOG specific changes in various frequency bands of interest, including alpha, beta and theta up to 5 s prior to FOG onset (Handojoseno et al., 2012, 2015b; Shine et al., 2014). To this end, we will compare FOG episodes vs. unimpaired walking through virtual doorways. Furthermore, we will analyze the connectivity of these dynamics across the brain regions involved. We expect to observe FOG-related changes in coherence, including increased theta coherence in fronto-central regions as reported previously (Shine et al., 2014).

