### Sample size

2.6

An *a priori* sample size estimation was conducted using G*Power (v.3.1.9.4) for a linear multiple regression, fixed model with R^2^ increase, assuming an alpha level of 0.05, a power of 0.80, one primary predictor, and a total of five predictors (including covariates). We selected a moderate to large effect size of partial R^2^ = 0.25 (i.e., f^2^ = 0.33), informed in part from findings of Handojoseno et al. (2015b) on EEG electrocortical activity changes associated with transitions to FOG episodes (Handojoseno et al., 2015b). Additionally, as we plan to assess multiple FOG trials per person and condition (up to 15 trials) and analyze them using linear mixed effects models, which typically have higher statistical power than traditional aggregated mean analyses, we anticipate achieving sufficient power to detect effects even if they are somewhat smaller than initially estimated. The selection of 15 FOG episodes is driven by Cockx et al. (2024), who reported a median of 15 FOG episodes per participant and observed significant effects on neurophysiological changes, suggesting that up to 15 FOG episodes per participant may serve as a reasonable benchmark for achieving sufficient statistical power in the analyses (Cockx et al., 2024).

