## Discussion

3

With this study we aim to investigate the neural mechanisms and pathways underlying FOG (RO1, RO2) and the effects of vibrotactile cueing (RO3). To achieve this, we will examine the neurophysiological correlates of FOG using ambulatory EEG and fNIRS measurements in virtual walking environments. Participants will walk on a treadmill while immersed in these environments, allowing us to study the neurophysiological changes related to FOG episodes. In addition, a vibrotactile cueing device will be used aiming to improve FOG. Thus, we will compare cued versus non-cued walking and investigate its influence on the frequency of FOG episodes and the associated changes in brain activation. For RO1, we anticipate that our study will reveal distinct neurophysiological correlates of FOG in PD. Building on previous research that has identified key brain regions, such as the frontal and central areas (Asher et al., 2021; Cao et al., 2021; Handojoseno et al., 2015b; Shine et al., 2014), and various hypothetical neural mechanisms (e.g., executive dysfunction and interference model (Bardakan et al., 2022)) that seek to explain the pathophysiology of FOG, we expect to observe similar findings while also gaining additional insights through our novel and more ecologically valid experimental design. For RO2, we specifically expect to observe neurophysiological changes across various frequency bands of interest, including alpha, beta, and theta, occurring up to 5 s prior to the observable behavioral manifestations of FOG episodes when approaching virtual automatic doorways (Handojoseno et al., 2012, 2013, 2015b). For RO3, we hypothesize that vibrotactile cueing will reduce the occurrence of FOG episodes through mitigation of the neurophysiological changes linked to FOG (cf. RO2). Specifically, we expect that the neural signatures related to FOG will be less pronounced during cued walking compared to non-cued walking when approaching doorways.

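### The FOG versus unimpaired contrast for RO1 and RO2 is not tied to cue state, so if cued and non-cued epochs are mixed, part of the cue's own effect can enter the signature that RO3 relies on

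*Protocol article*

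**What the plan says.** The Introduction sets RO1 as finding regions with "differential activation prior to the kinematic onset of FOG compared to normal, unimpaired walking". For RO2 it says "we will compare FOG episodes vs. unimpaired walking through virtual doorways". Section 2.4 (Outcomes) repeats the comparison with normal walking. None of these places states whether the walking is cued.

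In section 2.8.4 the dependent variables are to be "compared between FOG episodes and the corresponding period of unimpaired walking or turning". The section separates walking-FOG from turning-FOG and adds: "Each FOG type will be compared against its corresponding unimpaired movement". The models carry "relevant covariates, such as disease stage, motor symptom severity, prior experience with cueing", plus random effects for participants. Prior experience with cueing is a trait of the participant. The cue state of the epoch is not named.

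Section 2.3 (Intervention) alternates cued and non-cued trials within each participant, so that their numbers are equal. Section 2.6 (Sample size) expects FOG episodes from more than one setting: "as we plan to assess multiple FOG trials per person and condition (up to 15 trials"). In the Discussion the authors write: "we hypothesize that vibrotactile cueing will reduce the occurrence of FOG episodes". RO3, as set out in the Introduction, asks whether cueing attenuates the changes found under RO2, and compares the cued versus non-cued pattern with the FOG-specific one.

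**The concern.** If cueing works as hypothesised, a cued trial yields fewer FOG epochs and more unimpaired ones than a non-cued trial. When epochs from all trials are used without regard to cue state, the FOG side of the contrast is mostly non-cued and the unimpaired side is slightly more than half cued. The contrast is then partly a comparison of non-cued with cued walking. Random participant effects do not remove this, because cue state varies within the participant.

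The protocol itself considers a direct cortical effect of cueing likely. The Introduction expects vibrotactile cueing to act on parietal and central areas that are also implicated in FOG, and allows that it may work through separate, compensatory pathways.

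Two things are at stake. Regions or bands could be labelled FOG-specific when they partly reflect vibration. And RO3 would test the cue against a reference that already contains some of the cue's own effect with its sign turned round. That blurs the distinction the Introduction leaves open, between cueing that counteracts the FOG pathway and cueing that compensates by another route. The trial is described as confirmatory and EEG activity is the primary outcome.

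**Working it through.** **Plan's own figure.** The article gives no FOG rate, no expected reduction and no cue effect size, so there is nothing to reproduce on this point. The rates and effect sizes below are assumptions.

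**Inputs from the article.** Equal numbers of cued and non-cued trials (2.3); up to 2 × 4 = 8 trials (2.5); 10 doorways in the hospital scenario (2.8.1.1); 30 participants (Abstract); fewer FOG episodes expected under cueing (Discussion).

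**Formulas.** Let p be the FOG probability per passage without the cue and q the probability with it. With equal numbers of passages:

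- cued share of FOG epochs = q / (p + q)
- cued share of unimpaired epochs = (1 − q) / (2 − p − q)
- d = first share minus second share

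If F is the true FOG effect and C the cue's own effect, the mixed contrast estimates F + d·C. When q < p, d is negative.

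**Numbers for p = 0.30.**

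| Reduction under cueing | q | Cued share of FOG | Cued share of unimpaired | d | Leak if C is 0.5 SD in size |
|---|---|---|---|---|---|
| 30% | 0.21 | 0.21/0.51 = 0.412 | 0.79/1.49 = 0.530 | −0.118 | 0.06 SD |
| 50% | 0.15 | 0.15/0.45 = 0.333 | 0.85/1.55 = 0.548 | −0.215 | 0.11 SD |
| 70% | 0.09 | 0.09/0.39 = 0.231 | 0.91/1.61 = 0.565 | −0.334 | 0.17 SD |

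The leak has the opposite sign to C. For the same reductions, the size of d runs from 0.11 to 0.31 at p = 0.20 and from 0.15 to 0.40 at p = 0.50. With no reduction, d = 0.

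**Consequence for RO3.** Treat F and C as patterns over regions and bands. Projecting the cue pattern on the estimated signature gives C·(F + d·C) = C·F + d·|C|². With d negative, the second term is always negative, which pulls towards attenuation even where C is unrelated to F. The sign of the total still depends on C·F.

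**Simulation.** 30 participants, 8 alternating trials of 10 doorways each (a simplification, since the city scenario has no such doors), p = 0.20, no true FOG effect (F = 0), within-participant difference in means, two-sided t test at 5%, 400 runs per setting. SD is that of a single epoch.

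| FOG rate ratio, cued/non-cued | C | Mean false signature | Rejection |
|---|---|---|---|
| 1.0 | −0.5 SD | 0.00 SD | 5% |
| 0.5 | −0.5 SD | +0.10 SD | 34% |
| 0.5 | −1 SD | +0.20 SD | 76% |
| 0.25 | −0.5 SD | +0.18 SD | 70% |
| 0.25 | −1 SD | +0.35 SD | 99% |

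With both sides kept to non-cued trials, the mean contrast was −0.008 to 0.007 SD and rejection 3% to 7%. That is compatible with 5%, given a Monte Carlo standard error of √(0.05 × 0.95/400) = 1.1 points. Stopping after the trial in which the total reached 15 FOG episodes left the false signatures almost unchanged, at +0.10, +0.19, +0.17 and +0.35 SD in the order of the last four rows. These are single tests without multiplicity correction. The correction planned in 2.8.4 would lower the rejection rates but would not remove the bias.

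**The case against.** The strongest reply is that the article never says cued and non-cued epochs are pooled. A reader might infer that it does, but the text only allows it. The word corresponding is not defined beyond motor context. If the comparator were drawn from the same trial, cue state would be matched automatically, since cueing alternates by trial, and a separate EEG recording per trial makes this feasible. The covariate list is open-ended. Section 2.3 counts FOG events in non-cued walking and refers to the sample size section, and 2.4 lists the cued versus non-cued comparison separately under RO3. Expecting FOG episodes per condition does not place cued episodes in RO1 or RO2, because RO3 needs them anyway.

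All of this is fair, and it is why the point is conditional. It does not close the gap. Section 2.8.4 states the comparator and names a matching rule, and an analyst following it could use all trials. The non-cued wording in 2.3 is a stopping rule for data collection, and 2.5 states that rule on total FOG episodes. An open covariate list commits to nothing about cue state.

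A second reply is that the size is speculative. This stands. The one study of tactile cueing and brain activity described in the Introduction reported no change in activation, though it covered only the prefrontal cortex. A 0.5 SD cue effect is illustrative, and leaks of 0.06 to 0.17 SD are modest.

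A reader might also infer that RO3 is bound to find attenuation, or that RO1 and RO2 cannot be answered. Neither follows. The bias has a direction but does not fix the result, and RO3 also uses percentage time frozen and gait measures, which this mechanism does not touch.

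**Conclusion.** The concern holds as a conditional one. As written, the RO1/RO2 contrast permits confounding by cue state. Bias arises only if three things hold together: epochs from both conditions are used without matching or adjustment, cueing lowers FOG frequency, and cueing has a cortical effect of its own. The second is the trial's hypothesis and the protocol considers the third likely, so the analysis text should not leave the first open.

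When all three hold, about 12% to 33% of the cue's own effect enters the signature with reversed sign, at an assumed non-cued FOG probability of 0.30 and reductions of 30% to 70%. RO3 is then biased towards apparent attenuation without being certain to find it. The bias disappears if any of the three fails.

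**What to change.** State in 2.8.4 which trials supply the RO1 and RO2 epochs, in one of two ways:

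- Match unimpaired epochs to FOG epochs on cue state within participant, and include cue state and its interaction with FOG as fixed effects.
- Or use FOG and unimpaired epochs from non-cued trials only, on both sides of the contrast.

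Under either choice, define the reference signature for RO3 from non-cued epochs only.

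The cost is a few sentences and no new data. The restricted version leaves fewer FOG episodes for RO1 and RO2; the matched version avoids that loss.

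Separately, sections 2.3 and 2.5 differ on which FOG events count towards 15 (those in non-cued walking, or all of them). The two passages must be reconciled, since the count affects how many non-cued episodes will be available.

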Lastly (RO3), we aim to investigate whether and how vibrotactile cueing influences the neural patterns associated with induced FOG and contributes to its reduction. We expect that vibrotactile cueing will attenuate the neurophysiological changes linked to FOG (identified in RO2), so that prior to passing doorways, FOG-specific neural signatures will be less pronounced during cued walking than during non-cued walking. Thus, we will evaluate the differential activation patterns of non-cued vs. cued walking through virtual doorways and compare them to FOG specific activation. Additionally, we will assess reductions in the percentage of time spent frozen and analyze corresponding changes in gait kinematics and kinetics.

As part of this research plan, we will consider interindividual differences in FOG kinematics, kinetics, and neural correlates, as well as in the effects of vibrotactile cueing, such as by differential stages of disease, motor symptoms severity, gender, emotional well-being and other well-described moderating factors.

This clinical trial will be performed as a series of confirmatory cross-over studies with people with PD suffering from FOG under the three main research objectives specified above.

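### RO2 estimates the FOG-versus-unimpaired difference in areas that RO1 selected with the same contrast in the same data, so its effect sizes are biased upward and it cannot independently confirm RO1

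*Protocol article*

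**What the plan says.** Statistical methods (2.8.4) sets out three linked steps.

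- **RO1** looks for cortical regions that differ before FOG onset. Brain activity is "compared between FOG episodes and the corresponding period of unimpaired walking or turning".
- **RO2** then describes the FOG signature, "focusing on the temporal and frequency dynamics within the cortical areas of interest as defined by the first part of our analysis". The Introduction gives RO2 its contrast: "we will compare FOG episodes vs. unimpaired walking through virtual doorways".
- **RO3** takes the result forward: "we will examine if and how vibrotactile cueing may alter the neural signatures of FOG described above". The Introduction words this step differently: "we will evaluate the differential activation patterns of non-cued vs. cued walking through virtual doorways and compare them to FOG specific activation".

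The Introduction calls the programme "a series of confirmatory cross-over studies", and Outcomes (2.4) makes the EEG measures of RO1 and RO2 primary. There is one sample of 30. Section 2.8.4 requires correction for multiple comparisons, with Bonferroni and cluster-based permutation as examples. No split sample, held-out data or cross-validation is described.

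**The concern.** An area enters RO2 because its FOG-minus-unimpaired difference was large enough in these participants and epochs to pass RO1. Part of that difference is chance. When RO2 estimates the same difference again in the same data, the chance part is still there, so the estimate is too large on average. A null area that passed RO1 by luck will also pass RO2 on the same measure. RO2 would then appear to confirm RO1 while adding no independent evidence. For primary outcomes in a study presented as confirmatory, effect sizes and p-values would not carry the meaning a reader gives them.

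The question extends to RO3 because it builds on the RO2 signature. If that signature was chosen for being large in non-cued walking, it may shrink in cued walking through regression to the mean alone.

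**Working it through.** **Inputs from the protocol.** n = 30 (Abstract); partial R² = 0.25, f² = 0.33, alpha 0.05 (2.6); 64 EEG electrodes (2.8.1.2); 46 long fNIRS channels (2.8.1.3).

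**Assumptions not in the protocol.** Ten regions as a coarse alternative to 46 or 64 sites; the same true effect at every site; Bonferroni selection; one FOG-minus-unimpaired contrast per participant; for RO3, 5 FOG and 15 unimpaired epochs per participant and condition with equal trial variance, and 25–100% of the contrast variance being trial noise.

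**1. Planning effect.** f² = R²/(1 − R²) = 0.25/0.75 = 0.33, as the protocol states. Read as a paired standardised difference, d = √0.333 = 0.577. The expected test statistic is λ = d√n = 0.577 × √30 = 3.16.

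**2. RO2 inflation, normal approximation.** With Bonferroni cut-off z, the selection probability is P = 1 − Φ(z − λ), and the mean estimate among selected sites, relative to the truth, is r = 1 + φ(z − λ)/(λP). For 10 sites z = 2.81, P = 0.64, and r = 1 + 0.375/(3.16 × 0.64) = 1.19.

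**3. RO2 inflation, simulated with t-tests.**

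| Sites | r, normal | r, t-test | Areas from independent data |
|---|---|---|---|
| 10 | 1.19 | 1.21 | 1.00 |
| 46 | 1.27 | 1.30 | 1.00 |
| 64 | 1.29 | 1.32 | 1.00 |

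A stricter correction gives more inflation, so multiplicity control does not cure it. What it does do is keep the chance of any false RO1 area at about 5%. With smaller true effects r rises: in a setting with 27 features (9 areas × 3 bands), about 1.6 at d = 0.4 and 2.1 at d = 0.3. Neither effect is in the protocol.

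**4. RO3 with no cueing effect, signature selected in non-cued data, FOG-minus-unimpaired compared.** The excess in the non-cued estimate is (r − 1)d. Only its trial-noise share w fails to recur under cueing, so the apparent attenuation is w(r − 1)/r.

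- Low end: w = 0.25, r = 1.21 gives 0.25 × 0.21/1.21 = 4.3%.
- High end: w = 1, r = 1.324 gives 0.324/1.324 = 24.5%.

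Simulation gives 4.3% and 24.5%, with false significant attenuation in 3.5–7.5% of tests against a nominal 2.5% in that direction.

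**5. RO3 under other readings.**

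- Signature selected from cued and non-cued data pooled: attenuation about 0, false significance 2.3–2.6%.
- All doorway passages compared: no bias, 2.4–2.7%. With equal trial variance, the mean over all passages is uncorrelated with the FOG-minus-unimpaired difference used for selection.
- Only unimpaired passages compared: slight bias the other way, 0.9–1.7%.

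**6. Which reading applies?** The protocol does not settle it. Intervention (2.3) counts the 15 FOG events in non-cued walking, which hints at non-cued selection; Participant timeline (2.5) counts a total without naming the condition. Section 2.8.4 speaks of the signatures, whereas the Introduction and Discussion speak of cued versus non-cued walking at doorways.

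**The case against.** **RO1 is spatial and RO2 temporal, so they are different tests.** Outcomes (2.4) does separate them in this way, and the calculation re-tests the identical measure, which is the worst case. But the same section describes both as changes in frequency bands, and both use the same contrast and epochs. What stands is that the full inflation applies to the same band-power or hemodynamic measures. Coherence, percentage time frozen and gait outcomes are not directly circular.

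**Correction for multiple comparisons is required throughout.** It is, and it limits false areas. A reader might infer that circular selection will produce many spurious areas; the documents do not support that. The harm is inflated size and non-independent confirmation.

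**The Introduction already names frontal and central regions, the alpha, beta and theta bands, and a 5 s window.** For bands and window this stands. For areas it does not, because 2.8.4 uses whichever areas RO1 yields.

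**A journal article condenses the full plan.** True, but the selection rule is stated here, and that rule is the problem.

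**RO3 need not be biased.** This stands in large part. A reader might infer that cueing is bound to look effective. That requires both non-cued selection and a FOG-minus-unimpaired comparison, and the protocol fixes neither. The doorway wording in the Introduction and Discussion allows a comparison with no such bias.

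**Conclusion.** The RO1-to-RO2 circularity is in the written plan. At the planning effect, RO2 estimates in the selected areas average about 1.2 to 1.3 times the truth. This rests on Bonferroni selection over 10 to 64 sites and on reading partial R² 0.25 as a paired effect of 0.58; cluster-based selection would give other figures. A twofold exaggeration might be inferred, but it needs true effects near 0.3, which the documents do not give. RO2 tests of the same measures should not be presented as independent confirmation of RO1.

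For RO3 the finding is conditional. Spurious attenuation of roughly 4–25%, with 3.5–7.5% false significance, arises only under the reading in step 4 of the working. It is absent if selection pools the conditions or all doorway passages are compared. The defect there is that the selection data and the contrast are left open.

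**What to change.** For confirmatory RO2 and RO3 tests, choose one of these before any data are analysed:

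- **Fixed areas.** Name the areas in advance from the regions already given in the Introduction, with the bands and 5 s window already named. Keep RO1 as a separate whole-head search, so that new activation in the virtual setting can still be found.
- **Leave-one-participant-out.** Select areas from the other 29 participants and score the one held out. These scores depend on one another, so test them by a permutation that repeats the selection each time.

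Otherwise, report RO2 estimates in RO1-selected areas as descriptive.

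For RO3, select the signature from data pooled over, or independent of, cueing condition, and state whether the test compares the FOG-minus-unimpaired signature or doorway passages. Sections 2.3 and 2.5 must be reconciled on which episodes count towards 15.

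The cost is analysis wording and code, a little more analysis work, and somewhat smaller effect estimates. Recruitment and data collection for this point are unchanged.
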